|------------------------------------|-------------------------------------------------------------------------------------------------------------------------------------------------------------------------------------------------------------------------------------------------------------------------------------------------------------------------------------------------------------------------------------------------------------------------------------------------------------------------------------------------------------------------------------------------------------------------------------------------------------------------------------------------------------------------------------------------------------------------------------------------------------------------------------------------------------------------------------------------------------------------------------------------------------------------------------------------------------------------------------------------------------------------------------------------------------------------------------------------------------------------------------------------------------------------------------------------------------------------------------------------------------------------------------------------------------------------------------------------------------------------------------------------------------------------------------------------------------------------------------------------------------------------------------------------------------------------------------------------------------------------------------------------------------------------------------------------------------------------------------------------------------------------------------------------------------------------------------------------------------------------------------------------------------------------------------------------------------------------------------------------------------------------------------------------------------------------------------------------------------------------------------------------------------------------------------------------------------------------------------------------------------------------------------------------------------------------------------------------------------------------------------------------------------------------------------------------------------------------------------------------------------------------------------------------------------------------------------------------------------------------------------------------------------------------------------------------------------------------------------------------------------------------------------------------------------------------------------------------------------------------------------------------------------------------------------------------------------------------------------------------------------------|
| STATISTICAL CONSIDERATIONS: | 
Collected data will be identified only by a volunteer identification number. At the end of the study, a full analysis will be prepared according to a pre-specified statistical analysis plan. All analyses will be based on the modified intention-to-treat cohort and will analyze volunteers according to the group to which they were randomized.
 
Safety and tolerability will be addressed by examining the overall rates of adverse events and serious adverse events that might be associated with FTC/TDF daily and FTC/TDF intermittent regimens. All clinical and routine laboratory data will be included in the safety analysis. With 24 volunteers assigned to daily or intermittent FTC/TDF, observing no drug-related serious toxicity would result in an exact, two-sided, 95% confidence interval of (0.0000, 0.1425). If one drug-related SAE is observed, the exact, two-sided, 95% confidence interval would be (0.0011, 0.2112).
 
The proportion of volunteers who took at least 80% of the study medication recorded using Medication Event Monitoring System (MEMS) data will be estimated. For the intermittent group, since the dosing frequency is dependent on sexual activity, data collection using cell phone communication will be used to determine daily sexual activity in order to determine the number of expected doses. Adherence will be expressed as overall percent adherence over the study interval, longitudinal adherence by month, and for the intermittent regimen, adherence to twice weekly scheduled doses and adherence to doses during days of sexual activity. With 36 volunteers (combining active and placebo for each regimen), this study will have 51% power to detect a true adherence rate of 90% for each regimen. Power increases to 90% if the true adherence rate is 95%.
 
The proportion of volunteers assigned to FTC/TDF with detectable plasma FTC/TDF levels within 48 hours of a MEMS event will be estimated. Levels of FTC/TDF in hair samples will be evaluated for exploratory purposes only.
 
Assuming intracellular drug level has a log-normal distribution with a between subject standard deviation of 1.0 on the natural logarithm scale, this study should have about 79% power to rule-out a two-fold or greater relative decrease in the geometric mean concentration due to intermittent versus daily FTC/TDF. If the between subject standard deviation is 0.5, then there will be about 80% power to rule-out a 1.5-fold or greater decrease in the geometric mean concentration.
 
Intracellular drug levels will be correlated with adherence data for volunteers assigned to FTC/TDF for each regimen.
 
Descriptive statistics will be used to describe changes in HIV risk behaviour. Assuming condoms are used always or frequently by 60% of volunteers at baseline, this study has 85% power to detect a decrease in condom usage by treatment group (n=24) if volunteers
 |
|------------------------------------|-------------------------------------------------------------------------------------------------------------------------------------------------------------------------------------------------------------------------------------------------------------------------------------------------------------------------------------------------------------------------------------------------------------------------------------------------------------------------------------------------------------------------------------------------------------------------------------------------------------------------------------------------------------------------------------------------------------------------------------------------------------------------------------------------------------------------------------------------------------------------------------------------------------------------------------------------------------------------------------------------------------------------------------------------------------------------------------------------------------------------------------------------------------------------------------------------------------------------------------------------------------------------------------------------------------------------------------------------------------------------------------------------------------------------------------------------------------------------------------------------------------------------------------------------------------------------------------------------------------------------------------------------------------------------------------------------------------------------------------------------------------------------------------------------------------------------------------------------------------------------------------------------------------------------------------------------------------------------------------------------------------------------------------------------------------------------------------------------------------------------------------------------------------------------------------------------------------------------------------------------------------------------------------------------------------------------------------------------------------------------------------------------------------------------------------------------------------------------------------------------------------------------------------------------------------------------------------------------------------------------------------------------------------------------------------------------------------------------------------------------------------------------------------------------------------------------------------------------------------------------------------------------------------------------------------------------------------------------------------------------------------------|

|  |                                                                                                                                                                                                                                                                                                                                                                                                                                                                                                                                                                   |
|--|-------------------------------------------------------------------------------------------------------------------------------------------------------------------------------------------------------------------------------------------------------------------------------------------------------------------------------------------------------------------------------------------------------------------------------------------------------------------------------------------------------------------------------------------------------------------|
|  | 
reduce the rate to 30%. A decrease to a rate of 40% would be detected with 49% power. Power is based on a two-sided, 0.05 level test of a binomial proportion.
 
Descriptive statistics will be used to describe acceptability, medication sharing, and HIV-specific immune responses. Assuming a 10% HIV-specific immune response rate in the combined placebo groups, this study will have about 83% power to detect an increased immune response rate due to intermittent PrEP if the true response rate is 50% in the intermittent FTC/TDF group.
 |
|--|-------------------------------------------------------------------------------------------------------------------------------------------------------------------------------------------------------------------------------------------------------------------------------------------------------------------------------------------------------------------------------------------------------------------------------------------------------------------------------------------------------------------------------------------------------------------|

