|                         | 
Acceptability:
 

• The proportion of volunteers who report willingness to use the study regimen

• The acceptability to the HIV-infected partner of their partner using the investigational product

 
Intracellular drug concentrations:
 

• The mean intracellular drug concentration for each group assigned to FTC/TDF

 
Adherence:
 

• The proportion of volunteers who took, by MEMS (Medication event monitoring system) data, at least 80% of expected doses of the investigational product

• The proportion of volunteers assigned to FTC/TDF who have detectable drug plasma levels within 48 hours of reported use.

• The relationship between intracellular drug levels and adherence in volunteers assigned to FTC/TDF

 
Behavioral:
 

• Reported number of steady and casual sex partners

• Frequency of unprotected vaginal intercourse

• Substance use prior to or during sex

 
Other:
 

• The proportion of volunteers who report somewhat high or high levels of burden in using electronic medication monitoring to measure adherence, and using cell phone communication to measure sexual activity

• The proportion of study days with missing sexual activity data

• The proportion of volunteers who report sharing medications

• The proportion of volunteers assigned to placebo who have detectable intracellular drug levels

• The proportion of HIV-infected partners in discordant couples not on ART with detectable drug levels

• The proportion of volunteers with HIV-specific immune responses as measured by analysis of cellular or humoral immune response, or changes in gene regulation as measured by microarray or proteomic techniques

 |                         |                |                         |         |       |    |         |              |    |         |       |    |         |              |    |

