**5.1.2 Other Endpoints**

- The proportion of volunteers who report somewhat high or high levels of burden in using electronic medication monitoring to measure adherence, and IVR or SMS to measure sexual activity
- The proportion of study days with missing sexual activity data
- The proportion of volunteers who report sharing study medication.
- The proportion of volunteers assigned to placebo that have detectable intracellular drug levels
- The proportion of volunteers with HIV-specific immune responses as measured by analysis of cellular or humoral immune response, or changes in gene regulation as measured by microarray or proteomic techniques

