#### **14.2.8 HIV-specific immune response**

HIV-specific immune responses will be measured at timepoints as specified in the Schedule of Procedures (Appendix A1). A volunteer will be considered to have a positive response if he/she has at least one positive test result prior to HIV infection. Fisher's exact test will be used to test for any difference in the response rate between intermittent or daily FTC/TDF and placebo recipients. Assuming a 10% HIV-specific immune response rate in the combined control group, this study will have about 83% power to detect an increased response rate due to intermittent PrEP if the true response rate is 50% in the intermittent FTC/TDF group.

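### The HIV-specific immune response proportion lists gene-expression or proteomic change as an alternative component without tying it to HIV antigen, so a drug effect or background variation can count as a response

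*Protocol*

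**What the plan says.** The synopsis (Endpoints, Other) and Section 5.1.2 define the endpoint in the same terms: "The proportion of volunteers with HIV-specific immune responses as measured by analysis of cellular or humoral immune response, or changes in gene regulation". The last component reads in full "or changes in gene regulation as measured by microarray or proteomic techniques". The three components are joined by 'or' within a single proportion.

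Section 14.2.8 supplies the responder rule: "A volunteer will be considered to have a positive response if he/she has at least one positive test result prior to HIV infection". It also supplies the analysis: Fisher's "exact test will be used to test for any difference in the response rate between intermittent or daily FTC/TDF and placebo recipients".

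The power statement is conditional. Section 14.2.8 reads "Assuming a 10% HIV-specific immune response rate in the combined control group" and gives about 83% power "if the true response rate is 50% in the intermittent FTC/TDF group". The synopsis (Statistical Considerations) says the same: "Assuming a 10% HIV-specific immune response rate in the combined placebo groups, this study will have about 83% power".

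Section 9.2.1 describes serum antibodies to HIV antigens by ELISA. Section 9.2.2 describes cellular responses to HIV peptide pools or sets, and calls the immune evaluations exploratory. The PBMC row of Appendix A1 refers to antibodies and cellular responses to HIV antigens. None of these places describes a microarray or proteomic assay.

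**The concern.** Read together, the endpoint definition and the responder rule form a union: a volunteer who is positive on any listed component is a responder. The union keeps the label HIV-specific only if every component is HIV-specific. The antibody and T-cell components are, by virtue of the antigen in the assay. A change in gene or protein expression is not HIV-specific by nature. It may follow the study drug, another infection, or variation between visits.

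Two errors become possible. Non-specific positives spread over both arms dilute a real difference. Expression changes caused by FTC/TDF occur only in the active arms, and the responder rule cannot tell them from HIV-specific immunity. Section 19.0 plans a primary manuscript on safety and immune responses, so a diluted or false result would be visible even though the endpoint is secondary in rank.

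**Working it through.** **Inputs from the protocol**
- Group sizes: 24 intermittent FTC/TDF and 24 combined placebo (Section 14.1).
- Response rates: 10% control and 50% intermittent FTC/TDF (Section 14.2.8).
- Test: Fisher's exact test (Section 14.2.8). Its level is not stated; two-sided 0.05 is assumed, as Section 14.2.6 states for its binomial test.

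**Method.** Power is the sum, over all 25 × 25 possible tables (a, b) with Fisher p ≤ 0.05, of Bin(a; 24, p₁) × Bin(b; 24, p₀), where p₁ is the active rate and p₀ the control rate.

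**Step 1. The plan's own figure.** With p₁ = 0.50 and p₀ = 0.10, power is 0.834. The stated value of about 83% is reproduced.

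**Step 2. Non-specific positives, equal in both arms.** Let q be the probability of a non-specific positive, independent of the HIV-specific response. The protocol gives no q; the values below are assumed. The union rates are p₀ = 1 − 0.9(1 − q) and p₁ = 1 − 0.5(1 − q), so the difference shrinks to 0.4(1 − q).

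| q (assumed) | Control | Active | Power |
|---|---|---|---|
| 0 | 10% | 50% | 0.834 |
| 5% | 14.5% | 52.5% | 0.7455 |
| 10% | 19% | 55% | 0.6645 |
| 20% | 28% | 60% | 0.530 |
| 30% | 37% | 65% | 0.413 |

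**Step 3. Expression change from the drug only.** Suppose HIV-specific responses are 10% in both arms, and FTC/TDF alone causes an expression change counted as positive in a share r of active recipients (also assumed). Then p₀ = 0.10 and p₁ = 1 − 0.9(1 − r).

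| r (assumed) | Active | Probability of a significant result |
|---|---|---|
| 0 | 10% | 0.017 |
| 10% | 19% | 0.082 |
| 20% | 28% | 0.2615 |
| 30% | 37% | 0.516 |
| 40% | 46% | 0.754 |

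**Step 4. Restricted endpoint.** If only antigen-specific cellular or humoral results count, and the 10% and 50% are kept for them, power stays at 0.834.

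**Opportunities for a positive.** The study summary in Section 3.7 speaks of 2 to 3 assessments; Appendix A1 collects PBMCs at Weeks 0, 4, 8, 12, 16 and 24. Because one positive is enough, each added assessment can only raise q.

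**The case against.** The strongest reply is that the phrase HIV-specific governs the whole list, so that microarray and proteomics are merely further ways of detecting HIV-specific responses. On that reading, only changes shown to be HIV-specific would count. A second reply is that Section 14.2.8 refers to tests scheduled in Appendix A1, which names no microarray or proteomic test, so such results may never enter the Fisher comparison. A third is that positivity criteria belong in the Laboratory Analytical Plan or the data analysis plan, neither of which is at hand.

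Much of this stands as a limit. A reader might infer that any change in gene regulation makes a volunteer a responder. The text does not say so. A reader might also infer that the 83% is wrong. It is not: it reproduces, and it is expressly conditional on an HIV-specific response rate of 10%. Nor do the documents support saying that the trial would report immune priming that did not occur. They give no rate of background expression change and none caused by FTC/TDF.

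What the replies do not remove is the ambiguity over which components form the proportion. That is fixed in the protocol itself, in two places, and no section links the third component to antigen stimulation. A cut-off chosen later would turn an expression change into a positive or a negative, but would not by itself make it HIV-specific.

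**Conclusion.** The point holds as a defect of definition. As worded, the endpoint and the responder rule allow an expression or proteomic change with no stated link to HIV antigen to count as an HIV-specific response. The direction of the harm is clear: dilution if such changes occur equally in both arms, a spurious difference if the drug causes them. The size is not known. The ranges of 75% to 41% power and 8% to 75% significant results rest wholly on assumed rates, on independence of the components, on 24 versus 24, and on a two-sided 0.05 level. The 83% stands for the antigen-specific assays under the stated 10% and 50%.

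Severity is minor. The endpoint is listed under Other, Section 9.2.2 calls the evaluations exploratory, the endpoint does not drive the sample size, and Section 3.7 defers any link with protection to a larger study.

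**What to change.** - In the synopsis endpoints, Section 5.1.2 and Section 14.2.8, limit the responder definition and the Fisher test to cellular or humoral responses to HIV antigens. Word it so that only antigen-specific readouts count, since Section 9.2.2 also mentions cell activation status without naming an antigen.
- List gene-expression and proteomic change as a separate exploratory outcome, reported by arm.
- In the synopsis statistical considerations and Section 14.2.8, state that the 10% and the 83% refer to the restricted definition.

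The cost is wording only: no assay, sample or visit is lost, and the stated power is unchanged under the protocol's own assumptions. The one thing given up is that gene-regulation data no longer contribute to the responder proportion.

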**ABBREVIATIONS**

| Abbreviation | Term                                 |
|---------------------|---------------------------------------------|
| AE                  | Adverse Event                               |
| AIDS                | Acquired Immunodeficiency Syndrome          |
| ALT                 | Alanine-Aminotransferase                    |
| ART                 | Anti-retroviral therapy                     |
| AST                 | Aspartate-Aminotransferase                  |
| CFC                 | Cytokine Flow Cytometry                     |
| CMI                 | Cell Mediated Immunity                      |
| CMV                 | Cytomegalovirus                             |
| CRF                 | Case Report Form                            |
| CTL                 | Cytotoxic T Lymphocyte                      |
| DCC                 | Data Coordinating Centre                    |
| DNA                 | Deoxyribonucleic Acid                       |
| ELISA               | Enzyme Linked Immunosorbent Assay           |
| FTC/TDF             | emtricitabine/tenofovir disoproxil fumarate |
| GCP                 | Good Clinical Practice                      |
| HAART               | Highly Active Antiretroviral Treatment      |
| HAV                 | Hepatitis A Virus                           |
| HBV                 | Hepatitis B virus                           |
| HIV                 | Human Immunodeficiency Virus                |
| HLA                 | Human Leukocyte Antigen                     |
| HSV                 | Herpes Simplex Virus                        |
| IAVI                | International AIDS Vaccine Initiative       |
| ICH                 | International Conference on Harmonization   |
| IEC                 | Independent Ethics Committee                |
| IVR                 | Interactive Voice Response                  |
| Kg                  | Kilogram                                    |

| Abbreviation | Term                                     |
|---------------------|-------------------------------------------------|
| MEMS®               | Medication event monitoring system              |
| mg                  | Milligram                                       |
| MSM                 | Men who have sex with men                       |
| NRTI                | non-nucleoside reverse transcriptase inhibitors |
| PCR                 | Polymerase Chain Reaction                       |
| Pfu                 | Plaque Forming Units                            |
| PBMC                | Peripheral Blood Mononuclear Cells              |
| PrEP                | Pre-Exposure Prophylaxis                        |
| iPrEP               | Intermittent Pre-Exposure Prophylaxis           |
| RPR                 | Rapid Plasma Reagin                             |
| SAE                 | Serious Adverse Event                           |
| SIV                 | Simian Immunodeficiency Virus                   |
| SHIV                | Simian-Human Immunodeficiency Virus             |
| SOP                 | Standard Operating Procedure                    |
| SOM                 | Study Operations Manual                         |
| SRSV                | Small Round Structured Virus                    |
| SMS                 | Short Message Service                           |
| SRB                 | Safety Review Board                             |
| STI                 | Sexually Transmitted Infection                  |
| TDF                 | Tenofovir Disoproxil Fumarate                   |
| TPHA                | Treponema Pallidum Hemagglutination             |

